### Data analysis

Data will be coded and stored in a password-protected database and analyzed using a statistical software package (IBM SPSS Statistics version 20.0; IBM, Armonk, NY, USA). Study endpoints experienced for each treatment group will be formally analyzed on an intention-to-treat basis [36]. Important potential confounders will be included in a secondary multivariate analysis (e.g., hospital admission, mortality). Post hoc subgroup analysis will be used to further explore outcomes according to the intensity of the intervention and completeness of relevant personalized education received by intervention participants.

The study endpoints will be presented quantitatively (proportions, statistical differences between groups) and qualitatively (description of discrepancies, MRPs, and some patient-reported medication beliefs and illness perceptions). All tests will be two-tailed, and significance will be set at α = 0.05. Continuous and normally-distributed variables will be presented as mean ± SD. Differences between groups will be analyzed using one-way analysis of variance. Non-normally distributed data will be presented as median (range), and nonparametric tests will be used to analyze differences between groups. Categorical data will be analyzed using Pearson’s chi-square test or Fisher’s exact test. Pearson’s correlation or Spearman’s rank correlation coefficient will be used to identify linear relationships between normally distributed and non-normally distributed continuous variables, respectively.

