Time to first episode of decompensation and time to death (cause-specific and all-cause) will be assessed using Kaplan-Meier survival curves. The curves will be compared with the log-rank test statistic. Cox proportional hazards modeling will be used to calculate HRs, after testing the proportional hazards assumption. Patients will contribute person-time from the date of recruitment until the earliest of end of follow-up (12 months) or death (date of death to be obtained from medical records). Competing risks analysis will be performed in which we encode, as separate events, time to first readmission with a cirrhosis-related episode, death resulting from cirrhosis, or death resulting from other causes. This will be extended to multivariate analysis if there are a sufficient number of events.

It is anticipated that a proportion of participants (approximately 30%) will be lost from the study before completing follow-up assessments at *t*
_3_. Although the sample size calculation has been adjusted to accommodate for this loss, subjects who have completed only one assessment will be included in the analyses to establish baseline parameters in both treatment groups. With respect to changes from baseline, data imputation will be considered. In decompensated cirrhosis, dropouts due to death are informatively censored, and thus the responses of patients with missing data will be modeled explicitly. Subjects will be matched using baseline demographic and patient-reported outcomes, repeating this technique for both intervention arms. Imputation methods such as a hot-deck imputation and iterative regression imputation will be used. The sensitivity of the results to each of these methods will be assessed to quantify the degree of bias present.

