### Power calculation and sample size determination

On the basis of a primary endpoint of a 50% reduction in medication discrepancies (3.12 ± 2.5 per patient [6] to 1.56 per patient), 41 participants will be required per treatment arm to achieve ≥80% statistical power. Median survival in decompensated cirrhosis is 2 years [37]. Therefore, a 6-month mortality rate between 10% and 15% among the study cohort is predicted. The Hepatology Outpatient Centre’s attendance failure/reschedule rate is approximately 20%. Therefore, a possible 30% loss will be accounted for, and at least 106 participants will be recruited.

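### The plan calls dropout through death informative, names imputation methods that treat it as explained by baseline, and expects a comparison of those methods to quantify the bias

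*Protocol article*

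**What the plan says.** All of this is in the protocol article.

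- **Data analysis, on the mechanism.** About 30% of participants are expected to be lost before t3. The text says that "dropouts due to death are informatively censored, and thus the responses of patients with missing data will be modeled explicitly".
- **Data analysis, on the method.** Imputation is to be considered for changes from baseline. Patients are to be matched on baseline demographics and patient-reported outcomes, separately in each arm. Then: "Imputation methods such as a hot-deck imputation and iterative regression imputation will be used".
- **Data analysis, on the check.** "The sensitivity of the results to each of these methods will be assessed to quantify the degree of bias present".
- **The section that sets the recruitment target (Power calculation and sample size determination).** "a 6-month mortality rate between 10% and 15% among the study cohort is predicted", alongside a clinic "attendance failure/reschedule rate is approximately 20" percent. A 30% loss is allowed for and at least 106 participants are to be recruited.
- **Study endpoints and data collection.** Loss to follow-up for the t3 survey is defined by two missed appointments. No separate rule is given for patients who have died.

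**The concern.** The premise and the method do not fit. If dropout through death is informative, survivors with the same baseline values do not show what the missing responses would have been. Yet a hot-deck donor must have a t3 value, so every donor is alive at t3, and a regression for t3 responses is fitted to the same patients. The named matching set also leaves out MELD score, decompensation history and hospitalization frequency, which the same section lists as variables that may influence the endpoints.

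There is a second difficulty for deaths. A discrepancy between reported and documented medications, an adherence score or a quality-of-life score does not exist after death. Filling one in answers a question that the plan has not posed.

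The sensitivity check then risks false reassurance. If hot-deck and regression give similar answers, a reader who follows the plan's wording will conclude that bias is small. Agreement is what one would expect from two methods with the same assumption, whatever the bias. The primary outcome, discrepancies at t3, is among those affected.

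**Working it through.** **Step 1: the plan's own figure.** Inputs from the power section: difference 3.12 − 1.56 = 1.56, SD 2.5, power at least 80%. From Data analysis: two-sided α = 0.05.

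n per arm = 2 × (1.96 + 0.8416)² × 2.5² / 1.56² = 2 × 7.849 × 6.25 / 2.4336 = 40.3, rounded up to 41. The stated 41 is reproduced (power 80.7% by the normal approximation). The recruitment target is consistent with 82 × 1.3 = 106.6.

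**Step 2: how much of the missing data is death.**

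- Missing t3 records: 0.30 × 106 = 31.8, about 32.
- Deaths: 0.10 × 106 = 10.6 to 0.15 × 106 = 15.9, about 11 to 16.
- Share of the loss: 0.10/0.30 = one third, to 0.15/0.30 = one half.

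**Step 3: what each method assumes.**

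| Method | Learns from | Assumes |
|---|---|---|
| Within-arm hot-deck on baseline | patients with t3 data | missingness explained by the matching variables |
| Iterative regression | patients with t3 data | missingness explained by the model's predictors |

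The mechanics differ but the assumption is the same, and it is the one that the plan has just set aside for deaths.

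**Step 4: can the comparison detect the shared bias?** Suppose a fraction f of an arm dies, and their unobserved values exceed those of matched survivors by δ. Either method then misses the arm mean by −f × δ. The bias in the contrast (intervention minus control) is −(f_I × δ_I − f_C × δ_C), the same for both methods.

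Simulation assumptions: 53 per arm (1:1 allocation, inferred from equal arm sizes), means 3.12 and 1.56, SD 2.5, baseline-to-t3 correlation 0.5, 12.5% deaths plus 17.5% other loss, 1,500 runs. It compared a nearest-donor hot-deck with a stochastic regression imputation, both within arm. The values of δ and the correlation are assumed and do not come from the documents.

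| Scenario | Formula | Hot-deck bias | Regression bias |
|---|---|---|---|
| No shift | 0 | 0.014 | 0.014 |
| δ = 1.25, both arms | 0 | 0.016 | −0.004 |
| δ = 2.5, both arms | 0 | −0.003 | 0.009 |
| δ = 1.25, intervention only | −0.125 × 1.25 = −0.156 | −0.156 | −0.156 |
| δ = 2.5, intervention only | −0.125 × 2.5 = −0.313 | −0.324 | −0.318 |
| δ = 2.5, control only | +0.313 | 0.306 | 0.299 |
| δ = 2.5, both arms; deaths 15% control, 10% intervention | −(0.10 − 0.15) × 2.5 = 0.125 | 0.119 | 0.122 |

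The two methods differed by at most 0.02 on average in every row. That gap does not grow with the bias: it was largest (0.02) in a row where the bias was essentially nil. A bias of about 0.3 is 0.3/1.56, about 20% of the target effect.

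**The case against.** **The text is not a closed commitment.** Imputation is introduced as something to be considered, for changes from baseline, and the two methods are given as examples. The primary comparison at t3 is not expressly said to use imputed data. This stands, and it rules out saying that the t3 estimate will certainly contain values for patients who died. But the following sentences say that the methods will be used, and the sentence on informative death sits inside the imputation plan. Imputing for the dead is therefore the plain reading.

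**Explicit modeling could mean a not-at-random model.** It could, but none is described. The only methods named condition on baseline.

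**Deaths are analysed elsewhere.** Kaplan-Meier, Cox and competing-risks analyses are planned, so mortality by arm will be seen. Those analyses cover time-to-event outcomes and do not settle discrepancies, adherence or quality of life at t3.

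**The bias sizes are hypothetical.** This is fair. If no t3 value exists after death, there is no true value to be biased against. The simulation gives the dead a notional value in order to test the comparison. The figure of 0.3 needs a shift of one SD in one arm only. It falls to about 0.12 with the same shift in both arms and 15% against 10% mortality, and nearly cancels when deaths and shifts are equal. What does not depend on these sizes is that the comparison fails to register the bias.

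**Conclusion.** The point holds. The plan names informative dropout, offers methods that assume it away, and claims that comparing them will measure the resulting bias. The comparison can show only sensitivity to the choice of imputation method. About 11 to 16 of about 32 expected missing t3 records are deaths for which the outcomes are undefined and no separate handling is given. That count rests on the plan's predicted mortality, 30% loss and 106 participants. The size of any bias is unknown.

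A reader might also infer that the confidence intervals will be too narrow and the type I error inflated, because no combining rule for multiple imputations is mentioned. The document does not support that. It never says that imputation will be single or that imputed values will be analysed as observed, and the number of imputations is a detail that an article commonly leaves to the analysis plan. The inflation comes from a single fill-in: in a check under no effect, regression imputation drawn 20 times and pooled kept the error at 4–5%.

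**What to change.** 1. **Separate deaths from other missing t3 data.** Do not impute t3 discrepancies, adherence or quality of life for patients who died.
2. **State the target effect for patients who die before t3.** One option is a composite that ranks death as the worst outcome, reported beside the comparison in those alive at t3, with deaths by arm. Note that the alive-only comparison conditions on survival after randomization, which hypothesis H8 says the intervention may change. Randomization does not protect it, so it should not stand alone.
3. **For living non-responders, use multiple imputation.** Include arm, the baseline value of the outcome and the severity measures already collected (MELD, decompensation history, prior admissions).
4. **Replace the hot-deck-versus-regression comparison with a delta-adjusted analysis.** Shift the imputed values by stated amounts, separately in each arm, and report how far the conclusion moves.
5. **Reword the claim.** Describe the result as sensitivity to stated assumptions, not as a quantified bias.

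The cost is analysis-plan wording, some extra analysis and possibly wider intervals. No new data collection is needed. The alternatives in item 2 are choices for the investigators. What matters is that one is fixed before the t3 data are compared by arm.

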### Power calculation and sample size determination

On the basis of a primary endpoint of a 50% reduction in medication discrepancies (3.12 ± 2.5 per patient [6] to 1.56 per patient), 41 participants will be required per treatment arm to achieve ≥80% statistical power. Median survival in decompensated cirrhosis is 2 years [37]. Therefore, a 6-month mortality rate between 10% and 15% among the study cohort is predicted. The Hepatology Outpatient Centre’s attendance failure/reschedule rate is approximately 20%. Therefore, a possible 30% loss will be accounted for, and at least 106 participants will be recruited.

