**Fig. 1 Fig1:**
[figure not shown]
Standard Protocol Items: Recommendations for Interventional Trials (SPIRIT) flow diagram of participant recruitment and study navigation. *MRP* Medication-related problem

All participants will complete a baseline survey prior to their scheduled outpatient clinic review. Validated questionnaire tools will be used to determine baseline medication adherence, medication beliefs, illness perceptions, and QoL, in addition to patient knowledge of important dietary and lifestyle modifications. The survey will be completed with a study coordinator over the telephone or in person in a private clinic room, or it will be self-completed by the participant in the clinic waiting room. Patient carers or family members will be involved if necessary.

Usual care participants will subsequently receive routine review and education by their hepatologist according to the current model of care in the hepatology clinic. Intervention participants will be reviewed by a clinical pharmacist to receive the education and medication management intervention (described below) in addition to routine review and education by their hepatologist. Intervention participants will also receive three further educational contacts from the clinical pharmacist in addition to scheduled routine hepatologist review within the following 6-month period.

All participants will be resurveyed at follow-up (*t*
_3_, approximately 6 months post-enrollment) to explore changes in their medication adherence, medication beliefs, illness perceptions, QoL, and knowledge. Patient outcome data will be collected at 52 weeks (*see* “Study endpoints and data collection” section below).

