### Study endpoints and data collection

Study outcomes, tools, and time points for measurement are outlined in Table 3. Follow-up will occur approximately 6 months post-enrollment (allowed range 140–224 days after baseline interview), according to outpatient hepatology scheduling availability. If a follow-up appointment is missed, a second appointment will be offered to the patient within the allowed time frame. If the second appointment is missed, the patient will be considered lost to follow-up for *t*
_3_ survey endpoints.

**Table 3 Tab3:** Outcomes and other measures of the medication management and education intervention

Categories/variables	Measure	Collection week
Medication discrepancies		
Between drug name and dosage Frequency of per-patient discrepancies Severity of discrepancies	Patient interview Questionnaire Medical record review	*t* _0,_ *t* _3_
Medication-related problems (intervention arm only)		
Adverse drug reaction Drug interaction Untreated, undertreated, or overtreated indication Other medication-related barriers	Patient interview Questionnaire	*t* _0,_ *t* _3_
Adherence		
Self-reported medication adherence Affordability	MMAS-8 Patient interview	*t* _0,_ *t* _3_
Quality of life		
Health-related quality of life Abdominal and systemic symptoms Emotional functioning, fatigue, and worry Daily activity	CLDQ Brief IPQ	*t* _0,_ *t* _3_
Beliefs and perceptions		
General medication beliefs Beliefs about liver disease medications Illness perceptions	BMQ-General BMQ-Specific Brief IPQ	*t* _0,_ *t* _3_
Knowledge/health literacy		
Knowledge of causation Dietary modification including sodium restriction Self-monitoring requirements Safe analgesia Source of medication-related information	Questionnaire Brief IPQ	*t* _0,_ *t* _3_
Hospitalization		
Liver-related hospitalization Non-liver-related hospitalization Duration of stay	Medical record review	*t* _3,_ *t* _4_ (and 3 years)
Survival		
Liver-related mortality Non-liver-related mortality	Medical record review	*t* _3,_ *t* _4_ (and 3 years)
Cost		
Cost of service implementation Potential cost savings	Cost modeling	After study completion

*Abbreviations: BMQ* Beliefs about Medicines Questionnaire, *Brief IPQ* Brief Illness Perception Questionnaire, *CLDQ* Chronic Liver Disease Questionnaire, *MMAS-8* Eight-question Morisky Medication Adherence Scale

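### The recruitment target of 106 does not leave 41 participants per arm after the plan's own 30% loss; at that target and loss, power is about 75% to 77%, not at least 80%.

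*Protocol article*

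**What the plan says.** The section on power calculation and sample size (protocol article) bases the calculation on a "50% reduction in medication discrepancies (3.12 ± 2.5 per patient [6] to 1.56 per patient") and concludes that "41 participants will be required per treatment arm to achieve ≥80% statistical power". It then predicts 10% to 15% mortality at six months, cites a clinic attendance failure or reschedule rate of about 20%, and ends: "Therefore, a possible 30% loss will be accounted for, and at least 106 participants will be recruited".

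The Data analysis section says what the loss means. It expects that "a proportion of participants (approximately 30%) will be lost from the study before completing follow-up assessments" at t3, and continues: "Although the sample size calculation has been adjusted to accommodate for this loss". The same section fixes the test conditions: "All tests will be two-tailed, and significance will be set at α = 0.05".

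The primary outcome section examines discrepancies at baseline and at t3, and the Data analysis section compares the arms at those times. The t3 loss therefore falls directly on the primary endpoint.

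**The concern.** Two sections say that the target covers a 30% loss. That holds only if 106 recruits, less 30%, still leave 82 participants with t3 data. They do not. The figure looks like the common slip of multiplying the required number by one plus the loss, when it should be divided by one minus the loss.

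What is at stake is how the primary result is read. A null finding would be set against a stated power of at least 80%, whereas the plan's own inputs give a type II error of roughly 23% to 25% at the stated target. The slip does not bias the estimate and does not change the endpoint or the test.

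**Working it through.** **Inputs from the protocol article**
- Means 3.12 and 1.56 discrepancies per patient, so a difference of 1.56 (Power calculation).
- SD 2.5, given only for the mean of 3.12. I assume it applies to both arms.
- Two-sided alpha 0.05 (Data analysis).
- Target power at least 80%, 41 per arm, loss 30%, recruitment at least 106 (Power calculation).
- Equal allocation, implied by the single per-arm number.

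**Step 1. Reproduce the 41.** Normal formula: n per arm = 2 x SD² x (1.960 + 0.842)² / difference² = 2 x 6.25 x 7.849 / 2.4336 = 40.3, rounded up to 41. The plan's figure reproduces exactly. Power at 41 per arm is 80.7% by the normal formula and 79.7% by the noncentral t, which would ask for 42. That one-patient difference is not part of this point.

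**Step 2. Find where 106 comes from.**
- 82 x 1.3 = 106.6, rounded down to 106 (equivalently 41 x 1.3 = 53.3, taken as 53 per arm).
- Correct inflation: 82 / 0.70 = 117.1. Per arm, 41 / 0.70 = 58.6, rounded up to 59, so 118 in total. Check: 59 x 0.70 = 41.3.
- The target is 118 - 106 = 12 short.

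**Step 3. What 106 leaves.** 106 x 0.70 = 74.2, about 74, or 37 per arm. That is 8 fewer than 82.

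**Step 4. Power at 37 per arm.** Standard error = 2.5 x sqrt(2/37) = 0.581; 1.56 / 0.581 = 2.68.
- Normal formula: 76.5%.
- Noncentral t, 72 degrees of freedom: 75.4%.

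**Step 5. The loss that 106 can absorb.** (106 - 82) / 106 = 24 / 106 = 22.6%.

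**Step 6. Power by loss at 106 recruited** (numbers per arm not rounded)

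| Loss | Completers per arm | Power, t | Power, normal |
|---|---|---|---|
| 20% | 42.4 | 81.1% | 81.9% |
| 25% | 39.8 | 78.4% | 79.4% |
| 30% | 37.1 | 75.5% | 76.7% |
| 35% | 34.5 | 72.3% | 73.6% |

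Neither the choice of t or normal formula nor rounding makes 106 leave 41 per arm after a 30% loss.

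**The case against.** **The target is a floor.** The wording is at least 106, recruitment is reported complete, and the number enrolled is not given. A reader might infer that the trial itself has only 75% power. The documents do not support that, since enrolment may have passed 106. What stands is that 106 is offered as sufficient for a 30% loss and is not.

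**The real loss may be below 30%.** A reader might also infer that 30% is too low, since 10% to 15% deaths combined with 20% non-attendance give 28% to 32% if multiplied. That does not follow. The 20% includes rescheduled visits, and a second appointment within the window is offered; only then does the rule apply that "If the second appointment is missed, the patient will be considered lost to follow-up for" the t3 survey endpoints. If 45% of those who miss the first appointment also miss the second (my assumption; the documents give no figure), the loss is 1 - 0.90 x 0.91 = 18.1% to 1 - 0.85 x 0.91 = 22.7%, about what 106 can absorb. So 30% may well be on the pessimistic side. This weakens any prediction of an actual shortfall, but it does not reconcile 30% with 106, and both sections commit to 30%.

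**The SD may differ between arms.** At 37 per arm, an intervention-arm SD of 2.25 gives 79.5% power (t), and 2.0 gives about 83%. This is plausible for a count whose mean is halved, and it is why the 75% to 77% must carry its assumption. But the plan's 41 reproduces with SD 2.5 in both arms. With 2.0 in one arm the same formula would ask for (6.25 + 4.00) x 7.849 / 2.4336 = 33.1, or 34 per arm. The common SD is therefore the one consistent with the plan's own figure.

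**Imputation may help.** The plan says that imputation will be considered for changes from baseline. The sample size was justified by recruiting extra participants, and imputation cannot be assumed to restore the information of observed outcomes.

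**Conclusion.** The point holds as an arithmetic error in a stated figure. The 30% allowance was added to the number of completers needed; it should have been taken out of the number recruited. At the stated minimum of 106 and the stated loss of 30%, about 37 per arm remain against the 41 required, and power is about 75% (t test) to 77% (normal formula) against at least 80%. The loss of power from the slip itself is about 4 percentage points by either formula (79.7% to 75.4%, or 80.7% to 76.5%).

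The result assumes a common SD of 2.5, equal allocation, and a comparison of means in completers. It is moderate in size, and it says nothing about the power actually achieved or about whether 30% was the right loss to expect.

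**What to change.** Correct the sentence in the power section and the matching statement in Data analysis. Either of two wordings would be accurate:

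- With 106 recruited and 30% lost before t3, about 37 per arm are evaluable and power is about 75% to 77%, assuming a common SD of 2.5; a target of 118 would have been needed to keep 41 per arm.
- A target of 106 preserves 41 per arm only for losses up to about 22%.

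In the report, read a null primary result against the corrected figure and give the number actually enrolled and evaluable in each arm. No further enrolment is asked for, and the follow-up rules need not change to correct this statement. The cost is a sentence or so in each section and a slightly less favourable power figure.
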